### Data and Safety Monitoring

Adverse events are collected at every study visit and the site investigator rates their relationship to medication. Serious adverse events are defined as by the Therapeutics Goods Administration (TGA).^62^ If serious or unexpected adverse events occur during the trial, they are reviewed by the principal investigator and the trial team and reported within the specified time frames to the lead hospital ethics review committee (ERC) and to the Data and Safety Monitoring Board (DSMB). The DSMB comprises three members independent of the research study and funding body and meets regularly to provide oversight and monitoring to ensure participant safety and trial validity and integrity. The DSMB can request that the trial be terminated by the principal investigator in the event of safety concerns. Participants are assigned a code and their information de-identified in password-protected documents.

### Outcomes

*Primary outcome:* The primary outcome is alcohol consumption expressed as self-reported number of heavy drinking days per week, defined as >four drinks for women, >five drinks for men (where a single standard drink is defined by 10 g of ethanol). Any conflicting information will be validated by collateral reports and measurement of biological markers of alcohol consumption (PEth).

*Secondary outcomes:* Secondary alcohol outcomes include number of standard drinks per drinking day (SDDD) and absence of HDDs. We will also compare NAC vs PL on craving (ACEQ), alcohol dependence severity (ADS). Other secondary outcomes include adverse events, markers of liver injury (LFTs), levels of anxiety and depression (DASS), suicidal ideation (SIDAS), hangover symptoms (AHS), sleep disturbances (ISI) and cognitive functioning. We will explore the degree to which these clinical characteristics moderate treatment response and the mechanisms underlying these phenomena.

### Data analysis

*Sample size calculations:* A total of 180 AUD participants will be recruited for this study. We consider power for the primary outcome measure, HDD per week (analysed over 12 weeks). We regard Poisson means as approximately normally distributed, with variances equal to the means, adapting the methods of Hedeker *et al*.^63^ We consider power for a two-sided test at α=0.05, with n=180. We assume a within-subject correlation of 0.4, based on prior studies.^7^ For the effect of NAC vs placebo (treatment × time), we have >80% power to detect a small to medium effect where the groups separate to a small to medium effect (d=0.3) by week 12.

*Statistical analysis:* All available data from participants who took at least one dose of medication will be used to follow intention-to-treat principles. The primary outcome measure is frequency of HDDs (defined above), a sensitive, clinically relevant measure in alcohol trials.^64^ The two groups will first be compared for repeated measures of HDD frequency/week (weekly) using mixed effects models for count responses. Models can also be extended to allow for zero inflation, if patterns of abstinence yield more zero counts of HDDs than can be accommodated by a Poisson model. Secondary outcomes will also be examined using mixed models. Additional covariates and predictors will be included for sensitivity analyses. Categorical variables will be compared using a χ² test. Participants will be followed irrespective of whether they continue to receive treatment. As with all alcohol treatment studies, we anticipate some participant dropout and intermittent missing data which will be estimated through multiple imputation and assessed via sensitivity analysis.

*Cost-effectiveness analysis (CEA*): A cost-efficacy analysis will be conducted from both health sector and societal perspectives. As per our previous work, the primary outcome will be Quality Adjusted Life Years calculated from the Short Form 36. Participants will be consented for access to data on healthcare service use through Medicare and Pharmaceutical Benefits Schedules. A brief Health Services Use Questionnaire will capture additional resource use such as hospitalisations and lost productivity. Standardised economic evaluation techniques including incremental analysis of mean differences and bootstrapping to determine confidence intervals will be used. If the intervention is cost-efficacious, modelling techniques will be used to estimate the cost-effectiveness of NAC for the AUD population across Australia.

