### Patient recruitment

The trial is being conducted in several outpatient hospital and community settings across New South Wales, Queensland and Victoria, Australia. We aim to recruit up to 180 participants on a rolling basis through clinical referral (from treating clinicians of participating hospitals and community clinics) and via flyers/community advertisements in general practices, newspapers, websites (eg, Gumtree) and social media (eg, Facebook). Based on our previous experience, recruitment from mixed sources does not significantly impact treatment retention or outcome in alcohol pharmacotherapy trials.^34^ Participant time and travel expenses are reimbursed at the follow-up research assessments.

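### The power statement uses all 180 recruits as complete cases although the plan expects dropout; the stated >80% has almost no room for loss

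*Protocol article*

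**What the plan says.** The sample size paragraph (Data analysis) states the recruitment target: "A total of 180 AUD participants will be recruited for this study". It then uses that number for power: "We consider power for a two-sided test at α=0.05, with n=180". The Patient recruitment section makes 180 an upper limit: "We aim to recruit up to 180 participants on a rolling basis".

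The power claim is for the treatment × time effect on weekly heavy drinking days over 12 weeks: "we have >80% power to detect a small to medium effect", where "the groups separate to a small to medium effect (d=0.3) by week 12". The within-subject correlation is taken as 0.4. The distributional input is: "We regard Poisson means as approximately normally distributed, with variances equal to the means".

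The statistical analysis paragraph of the same section says: "As with all alcohol treatment studies, we anticipate some participant dropout and intermittent missing data". Missing values are to be multiply imputed. No dropout rate is given, and neither the sample size nor the power figure is adjusted for loss.

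The Introduction and the strengths and limitations box both describe the trial as well powered.

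**The concern.** One number does two jobs. It is the most the trial plans to enrol, and it is the number whose data support the power figure. The plan's own missing-data sentence says these will differ, so the stated power describes a data set that the authors do not expect to have.

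This matters most if the result is null. Readers would judge it against an effect of d=0.3 said to be detectable with more than 80% power. If realised power for that effect is in the mid-70s, the null says less than the article implies. The size of the problem depends on how much room the stated figure leaves above 80%.

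**Working it through.** **Inputs from the article:** n=180; two-sided α=0.05; correlation ρ=0.4; d=0.3 by week 12; weekly outcome over 12 weeks; treatment × time effect.

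**Inputs assumed because the article does not give them:** 1:1 allocation (90 per arm); compound symmetry; linear separation of the groups; d in units of the total SD, so SD=1; dropout rates of 10%, 20% and 30%.

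**Step 1. Reproduce the stated figure with complete data.** For a difference in linear slopes,

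SE = √[2(1−ρ)/(n_arm × Sxx)], z = slope difference/SE, power = Φ(z − 1.96).

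- Weeks 0–12 (13 points): slope difference 0.3/12 = 0.025; Sxx = 182; SE = √[1.2/(90×182)] = 0.00856; z = 2.92; power 83.2%.
- 12 weekly points, difference rising from 0 at the first to 0.3 at the last: slope difference 0.3/11 = 0.0273; Sxx = 143; SE = √[1.2/(90×143)] = 0.00966; z = 2.82; power 80.6%.

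Both agree with a claim of more than 80%.

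**Step 2. Room for loss.** 80% power needs z = 1.96 + 0.84 = 2.80. The number of complete participants required is 180 × (2.80/z)², using unrounded values: 165.6 and 177.1, so about 166–177. The tolerable loss of whole participants is 1 − 165.6/180 = 8.0% and 1 − 177.1/180 = 1.6%.

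**Step 3. Power under assumed dropout.** If dropouts contribute no data, z is multiplied by √(1 − dropout). If partial data are kept, I let dropout accrue evenly over the weeks and summed the generalised least squares information from complete and truncated series. In each cell the first figure is for 12 points and the second for 13.

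| Assumed dropout | Partial data kept | No data from dropouts |
|---|---|---|
| 0% | 80.6%, 83.2% | 80.6%, 83.2% |
| 10% | 77.7%, 80.4% | 76.4%, 79.1% |
| 20% | 74.4%, 77.2% | 71.4%, 74.3% |
| 30% | 70.7%, 73.5% | 65.7%, 68.6% |

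**Step 4. Detectable effect.** The d that gives 80% power is 0.3 × 2.80/z. At 20% dropout with partial data kept, z = 2.617 (12 points) and 2.706 (13 points), so d = 0.32 and 0.31. With complete data it is 0.30 and 0.29.

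**Step 5. Overdispersion, as a sensitivity only.** Suppose d was set in units of the square root of the mean and the model is conditional Poisson with a random intercept. A correlation of 0.4 then implies a marginal variance of mean/(1 − 0.4) = 1.67 × mean, and z is multiplied by √0.6 = 0.775. This gives z = 2.26 and 2.19, and power of 62% and 59% with no dropout.

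**Other readings.** Separation from baseline at 0.025 per week with only weeks 1–12 in the test gives 73.5% before any loss. A first-order autoregressive correlation gives 39–40% for the two variants in Step 1. A constant difference of 0.3 analysed as a time average gives 85.1%, falling to 76.5% if 20% contribute no data. The first two do not reproduce the claim, and the third is not the treatment × time effect that the article names.

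**The case against.** The strongest reply is that stopping treatment is not the same as losing outcome data. The article plans assertive follow-up of everyone randomised, by telephone if needed. Drinking is collected by 30-day timeline follow-back and by daily smartphone records, and all available data enter the mixed model. This stands as a reason to prefer the partial-data column and to treat whole-participant loss as the worst case. It does not remove the point, because the article still expects missing data after describing these measures. Multiple imputation does not put back information that was never collected.

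It is also fair to say that the stated figure contains no arithmetic error, that the cited method cannot be inspected here, and that the shift in detectable effect is small: d=0.31–0.32 is still small to medium. In the more favourable variant, 10% attrition with partial data kept leaves 80.4%. All of this stands and limits the size of the finding.

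A reader might infer more than the article supports:

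- **That the correlation of 0.4 contradicts variance equal to the mean.** It does not. Correlated counts with Poisson margins exist: simulated counts sharing a common Poisson component, with mean 3, had variance 3.0 and correlation 0.40. Weekly heavy drinking days are also bounded at 0–7. At mean 4, the binomial within-person variance is 4 × (1 − 4/7) = 1.71 and the total at correlation 0.4 is 1.71/0.6 = 2.86, below the Poisson value of 4. So even the direction of any error is not fixed.
- **That true power is as low as 50%.** That needs inflated variance, d on the square-root-of-mean scale and about 20% whole-participant loss together. The article states none of these.
- **That the contrast behind the power figure is unnamed.** The article says it is treatment × time. Power for a 12-week average under linear separation would be much lower, but the article does not specify that contrast.

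**Conclusion.** The point holds in limited form. The claim of more than 80% power reproduces at 80.6–83.2%, but only for close to complete data from all 180. It falls to 80% at a loss of about 2–8% of whole participants. With partial data kept it is about 78–80% at an assumed 10% attrition, 74–77% at 20% and 71–74% at 30%.

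These figures rest on 1:1 allocation, compound symmetry, linear separation and d in total SD units. The dropout rates are illustrations, since the article gives none, so no single figure can be called the true power. The 59–62% under overdispersion is conditional on a scale for d and a model that the article does not state; it is a sensitivity and not part of the finding.

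**What to change.** No additional enrolment is needed. In the sample size paragraph:

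1. State that 180 is the number randomised, give an assumed dropout rate with its basis, and report power for d=0.3 at that rate. Alternatively, report the effect detectable with 80% power, about d=0.31–0.32 at 20% dropout with partial data kept.
2. State the scale on which d is defined (total SD or square root of the mean) and the correlation structure used. If the scale is the square root of the mean, show an overdispersed sensitivity beside the main figure.
3. Qualify the description of the trial as well powered, in the Introduction and in the strengths and limitations box, to match the restated figure.

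The cost is wording only, plus a slightly less favourable stated power. Recruitment is still under way according to the article, so the restatement can be made before results are known.

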### Randomisation and allocation concealment

The study is a double-blind, RCT with participants randomised to receive one of two possible medication arms. The study is conducted under double-blind conditions so that participants and study staff are unaware of medication assignment. A computer-generated random allocation to NAC or placebo will be provided by an independent service inbuilt to RedCap software and stratified by site, smoking, sex, alcohol-related liver disease and medications for mood disorders. This is provided to the Clinical Trials Pharmacist at each site for intervention allocation and medication dispensing. In the event of a medical emergency that requires knowledge of the treatment condition, the investigators can contact the pharmacist to break the randomisation code for that individual.

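### The primary HDD model should name baseline heavy drinking and the five stratification factors; the article places covariates only in sensitivity analyses and leaves two possible methods for absence of HDDs

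*Protocol article*

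**What the plan says.** In the Protocol article, Randomisation and allocation concealment, allocation is "stratified by site, smoking, sex, alcohol-related liver disease and medications for mood disorders". Under Data analysis the primary comparison is described as follows: "The two groups will first be compared for repeated measures of HDD frequency/week (weekly) using mixed effects models for count responses". No baseline or stratification term is named. The section's only sentence on covariates is "Additional covariates and predictors will be included for sensitivity analyses". Medical management follows the same pattern: participants who start outside psychotherapy are handled as covariates in sensitivity analyses.

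Study assessments provides a 30-day TLFB at baseline, so baseline HDD per week can be calculated.

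For the binary drinking outcome, Outcomes states "Secondary alcohol outcomes include number of standard drinks per drinking day (SDDD) and absence of HDDs". Data analysis then gives two instructions that could both apply to it: "Secondary outcomes will also be examined using mixed models" and "Categorical variables will be compared using a χ² test". The second does not say which variables it means.

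**The concern.** Factors important enough to stratify on are normally carried into the primary model. If they are left out, the balance achieved by design is not credited: the standard error still contains variance that stratification has removed from the treatment difference, and the test becomes conservative. Sex is tied to the outcome directly, because the HDD threshold differs by sex.

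Baseline HDD is the pre-treatment value of the primary outcome. Leaving it out of a comparison of levels gives up precision and leaves any chance imbalance in heavy drinking in the headline estimate.

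At stake are the precision of the main result and confidence that the covariates were fixed before unblinding.

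**Working it through.** **Inputs.** Data analysis gives "We consider power for a two-sided test at α=0.05, with n=180", within-subject correlation ρ = 0.4, and a treatment × time effect with separation d = 0.3 by week 12 at more than 80% power. Assumed here: 1:1 allocation (90 per arm; the ratio is not stated), unit variance, exchangeable correlation, no dropout, and the normal approximation to counts that the plan itself uses.

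**1. The plan's own power.** For a linear contrast c over the weeks, the per-person variance is (1−ρ)Σc².
- Weeks 1–12, separation rising from 0 to 0.3: Σc² = 143; effect = (0.3/11) × 143 = 3.9; variance = 0.6 × 143 = 85.8; z = 3.9/√(2 × 85.8/90) = 2.82; power = Φ(2.82 − 1.96) = 80.6%.
- Weeks 0–12: Σc² = 182; effect = (0.3/12) × 182 = 4.55; variance = 109.2; z = 2.92; power = 83.2%.

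The stated figure reproduces on these two readings.

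**2. Baseline HDD and the powered slope.** The covariance of the slope contrast with baseline is ρΣc = 0.4 × 0 = 0, so adjustment gains nothing. A 4,000-run simulation agrees: 80.7% unadjusted, 80.6% adjusted.

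**3. Baseline HDD and a comparison of levels.**
- 12-week mean: variance = (1 + 11 × 0.4)/12 = 0.45. One baseline week removes 0.4² = 0.16, leaving 0.29, a fall of 0.16/0.45 = 36%.
- At a constant d of 0.3: z = 0.3/√(2 × 0.45/90) = 3.00, power 85.1%; adjusted z = 0.3/√(2 × 0.29/90) = 3.74, power 96.2%.
- At a mean d of 0.15, which is what linear separation from 0 to 0.3 averages: 32.3% rises to 46.4%.
- Week 12 alone, d = 0.3: variance 1 falls to 0.84 (16%); power 52.1% rises to 59.3%.

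The 36% corresponds to a correlation of 0.4/√0.45 = 0.60 between baseline and the 12-week mean. If that correlation were only 0.3 to 0.5, the reduction would be 0.3² to 0.5², that is 9% to 25%.

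**4. Stratification factors.** Let R² be the share of between-patient variance in the tested summary that the factors explain. The article gives no value, so a range is assumed. With balance on the factors, the true variance of the treatment difference is (1−R²) times the variance that the unadjusted test uses. Starting from 80% power at R² = 0:
- type I error, unadjusted = 2[1 − Φ(1.96/√(1−R²))]
- power, unadjusted = Φ(0.84/√(1−R²))
- power, adjusted = Φ(2.80/√(1−R²) − 1.96)

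| Assumed R² | Type I error, unadjusted | Power, unadjusted | Power, adjusted | Points lost |
|---|---|---|---|---|
| 2% | 4.8% | 80.2% | 80.8% | 0.6 |
| 5% | 4.4% | 80.6% | 82.0% | 1.4 |
| 10% | 3.9% | 81.3% | 84.0% | 2.7 |
| 20% | 2.8% | 82.7% | 87.9% | 5.2 |

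By the argument in step 2, a factor whose effect is constant over time has no covariance with the slope. For a slope test, R² is therefore only the share of variation in slopes that the factors predict.

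**5. How far stratification balances.** If the four factors other than site are binary, each site has 2⁴ = 16 cells. With three sites (assumed, one per named state) there are 48 cells, or 180/48 = 3.75 participants each. With six sites there are 96 cells, or 1.9 each. Balance will be incomplete, so the table is closer to an upper limit on the conservatism, and some chance imbalance remains for the model to absorb.

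**6. Absence of HDDs.** It is a secondary outcome, so the sentence on secondary outcomes sends it to mixed models. It is also categorical, so the next-but-one sentence can be read as sending it to an unadjusted χ² test. Nothing in the section decides between them.

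**The case against.** The strongest reply is that nothing is excluded. The word additional may mean additional to terms already in the model, and baseline may enter a treatment × time model as a repeated measure. The article refers to a full protocol (version 8) that is not shown, and a covariate list is commonly left to that document or the SAP. A reader might infer that the analysis ignores baseline HDD and the strata; no sentence says so. What remains is that the article does say where covariates go, does so again for concurrent psychotherapy, and ties the five factors to no model.

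The second reply is that the effect the plan powers gains nothing from baseline adjustment. That is correct, and a reader who carries the rise from 85% to 96% over to the plan's power statement would be wrong: it needs d = 0.3 in every week and a test of the average. An average or endpoint contrast is still relevant, because the outcome is defined as HDDs per week and the Introduction reports that the pilot effect varied over time.

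The third concerns χ². A reader might infer that absence of HDDs is restricted to that test. The sentence names no outcome, and the article says elsewhere that safety will be analysed with categorical outcomes, which is another plausible use. Only the overlap stands.

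Finally, eligibility requires more than two HDDs per week and withdrawal management may precede baseline. Both could weaken the correlation of baseline with later drinking, which is why the 9% to 25% range is shown.

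**Conclusion.** The point holds as one of efficiency and chance imbalance; the treatment comparison is not biased. If the stated placement of covariates is followed, omitting the stratification factors makes the test conservative, by an amount that rests on the assumed R² and on how well the fine strata balance. Omitting baseline HDD forgoes a 36% variance reduction for the 12-week average or 16% for week 12, provided ρ = 0.4 carries back to the pre-treatment period, and forgoes nothing for the slope under exchangeable correlation. The documents do not support saying that the powered test loses precision through the omission of baseline, or that the binary outcome is certainly analysed unadjusted. For that outcome the finding is two overlapping instructions that need reconciling. The change is worth making because the data are already collected.

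**What to change.** In the primary model, prespecify baseline HDD per week from the TLFB and main effects of site, smoking, sex, ArLD and mood-disorder medication, pooling very small sites. If baseline is instead to be a repeated measure, say so. Use the same set in the secondary models, with each outcome's own baseline value added. Report the unadjusted model as a sensitivity analysis.

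For absence of HDDs, state one method: a covariate-adjusted logistic model (mixed if the outcome is repeated over time) using the same multiple imputations as the other outcomes. Say which variables the χ² test is for.

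The cost is SAP wording. With three sites (assumed) and four binary factors, the added terms number 1 + 4 + 2 = 7 for 180 participants. The article describes the trial as double-blind and still recruiting, so the covariates can be fixed now without suspicion of a data-driven choice.

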### Ethics and Dissemination

Ethics approval for the study has been granted by The Sydney Local Health District Ethics Review Committee (X21-0342& HREC2021/ETH11614). Participants are provided with an approved plain language information sheet and provide written content to participate. The protocol is version 8. The study involves off-label use of a registered medication in Australia such that approval for this trial has been given under the Clinical Trial Notification (CTN) scheme of the TGA. The trial is sponsored by Sydney Local Health District and was registered with the NIH clinical trials registry on 7 June 2022 (NCT05408247). Participants are advised of their right to seek compensation from the study sponsor in the event of harm arising from trial participation. Protocol amendments to the clinical protocol will be updated to the clinical trials registry following approval by the corresponding ethics review committee. The Consumer Advisory Group and trial participants will be kept informed about study process, the final results and a lay summary provided to study sites for distribution. The trial is now in the recruitment phase (expected completion: 2026). There are no restrictions on publication from the sponsor or other parties. Publications will be authored by the investigators and authorship offered according to NHMRC criteria. De-identified data will be available at request from the investigators.

